### Sample size

Based on a previous survey [28], we conservatively estimated that unintentional injury incidence among preschoolers aged 3–6 years old in the study sites over a 12-month period will be 30%. According to relevant reports [29], we estimated the effect size of the Safety Experience Room intervention will be 0.75 (incidence rate ratio) compared with a traditional educational intervention. An intra-class correlation (ICC) of 0.005 within a cluster size of 200 children per preschool was estimated [30, 31]. Nearly whole rural preschoolers stay enrolled in the same preschool throughout childhood, so we conservatively estimate a maximum attrition rate of 10% over the 12-month follow-up time period. Given these estimates, a minimum sample size of 2378 preschoolers is sufficient to achieve statistical power of 80% at the significance level of 0.05. Our preliminary surveys indicate most local rural preschools have 200 to 300 children, so 12 preschools will be adequate to recruit the needed sample size.

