### Secondary outcome measures

We will collect data concerning several secondary outcome measures, as detailed below.

Preschooler’s unintentional injury prevention knowledge for road traffic injury, falls, and drowning. This knowledge will be evaluated based on the learning content of the 6 educational themes children are exposed to in the Safety Experience Room. Table 3 lists 18 key items we will use to measure children’s unintentional injury prevention knowledge.Cost-effectiveness analysis (CEA). The calculation of CEA will follow the World Health Organization CHOosing Interventions that are Cost-Effective (WHO-CHOICE) approach to estimate population level effects of the interventions using a form of generalized cost-effectiveness analysis (GCEA) [35, 36].

**Table 3 Tab3:** Key unintentional injury prevention behaviors that preschoolers will learn for road traffic injury, falls, and drowning prevention

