### Formal data collection

Survey data regarding the primary outcome for both groups, injury incidents, will be collected at baseline and every 3 months throughout the 12-month follow-up time period. In coordination with the local education bureau, the preschools will organize a caregiver-teacher meeting every 3 months. The class teacher will send the online survey link and ask all caregivers to complete the survey at the caregiver-teacher meeting. All primary outcome data will be collected through online survey. If caregivers fail to complete the online questionnaire, the classroom teacher will contact them to collect the survey data.

Collection of secondary outcome data will be carried out at baseline for both groups and after the intervention group completes each safety-related theme course designed for the intervention group. Secondary outcome data will be collected simultaneously from the control group to maintain comparison between two groups, but we will not disseminate any correct answers or teachings to the children in the control group before the study ends to avoid contamination in that group. All secondary outcomes data will be collected via preschoolers playing an evaluation version of the interactive games that has different story plots from the teaching version and permits retention of evaluation results. The evaluation version of the interactive games will not include any modules that disseminate injury prevention information or display evaluation results to children. Administration of the assessment will occur in a quiet environment. Each child will complete the tasks individually in the Safety Experience Room, with other classmates staying in the classroom respectively during the evaluation.

In order to assess children in the control group, relevant hardware and software (the multimedia touchscreen computer with the evaluation version of interactive games installed) will be delivered to control preschools accordingly. Staff members and teachers will help children start and reset the interactive games as well as maintain a quiet evaluation environment during the evaluation process.

Before formal data collection, teachers involved in both groups will learn to operate the evaluation games. Teachers will enter each child’s ID number and supervise individualized data collection but will not communicate with children or see children’s evaluation results. All data will be stored in the game backend database.

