### Data analysis plan

Primary data analysis will employ an intention-to-treat (ITT) approach. Descriptive statistics will be calculated for socio-demographic variables and primary and secondary outcomes, including mean (or median) and standard deviation (or range and interquartile range) for continuous variables, and frequency and proportion for categorical variables. At each time point, Chi-square test and two-sample t-test (or Wilcoxon rank sum test if data are skewed) will be used to examine the differences in outcome measures between intervention and control groups for categorical and continuous variables, respectively. Trend tests or analysis of variance (ANOVA) will be used to detect within-group differences across the four follow-up visits.

We will also use Generalized Estimating Equation (GEE) and Generalized Linear Mixed Models (GLMM) to evaluate the overall effectiveness of the intervention after adjusting for socio-demographic variables, engagement, and baseline injury events. Both binary outcomes (whether experienced unintentional injury during the study period) and quantitative count outcomes (number of unintentional injury events and injury prevention knowledge score) at the individual level will be analyzed using these models. Zero-inflation models will be used when needed.

Missing values will be imputed using either the Expectation Maximization (EM) algorithm or Markov Chain Monte Carlo, as appropriate for the data. A per-protocol (PP) sensitivity analysis will be conducted to validate ITT results. All statistical analyses will be performed using the up-to-date version of R. All statistical tests will be two-sided, with the level of 0.05 considered statistically significant.

Subgroup analyses will be performed to assess the impact of socio-demographic factors on the intervention effectiveness, including sex and age of children, grade level of preschoolers, education level of preschooler caregivers, and household income per capita in the prior 12 months. Subgroup analyses will follow the same statistical strategies for primary analyses.

This study will be rigorously conducted, analyzed, and reported in accordance with the Standard Protocol Items: Recommendations for Interventional Trials (SPIRIT) 2013 statement [37] and the Consolidated Standards of Reporting Trials (CONSORT) 2010 statement [38].

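### The knowledge-score model adjusts for baseline injury events but not for baseline knowledge, although baseline knowledge is measured in both arms; the cost is precision on a secondary outcome

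*Protocol article*

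**What the plan says.** Under Secondary outcome measures, the Protocol article makes injury prevention knowledge a secondary outcome: "Table 3 lists 18 key items we will use to measure children’s unintentional injury prevention knowledge".

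Under Formal data collection it sets the timing: "Collection of secondary outcome data will be carried out at baseline for both groups". Collection is repeated after each theme course, with the control group assessed at the same times.

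Under Data analysis plan, GEE and GLMM are to estimate the overall effect "after adjusting for socio-demographic variables, engagement, and baseline injury events". The next sentence extends these models to binary and count outcomes and names the knowledge score: "quantitative count outcomes (number of unintentional injury events and injury prevention knowledge score) at the individual level will be analyzed using these models". The one after it allows zero-inflated models if they are needed. No section names baseline knowledge as a covariate, gives the knowledge score a model of its own, or says that its baseline value enters as a repeated measure.

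**The concern.** A child's own baseline score is the natural covariate for a later score on the same items. The plan collects it and then does not list it, while it does list a baseline variable that belongs to the injury outcome. This is more than an omitted detail, because the list is applied to the knowledge score by name.

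The trial randomizes 12 preschools, 6 per arm. With so few units, the arms can differ by chance in mean baseline knowledge. Without the baseline score in the model, part of that difference appears in the estimated effect, and the confidence interval is wider than it needs to be.

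A lesser matter is the outcome type. A score built on 18 items is grouped with injury counts, and a zero-inflated option follows directly. A number correct has a ceiling, which an unbounded count model does not respect.

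**Working it through.** **The plan's own figure.** The article states no figure for knowledge, only for the primary outcome: "a minimum sample size of 2378 preschoolers is sufficient to achieve statistical power of 80% at the significance level of 0.05". Inputs from Sample size: 30% against 0.75 × 30% = 22.5%, ICC 0.005, 200 children per preschool, 10% attrition.

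- Per arm, unpooled: (1.960 + 0.842)² × (0.30 × 0.70 + 0.225 × 0.775) / 0.075² = 536.34
- Design effect: 1 + 199 × 0.005 = 1.995
- Total: 2 × 536.34 × 1.995 / 0.9 = 2377.8, rounded up to 2378

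The figure reproduces exactly, and nothing below changes it.

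**Inputs for knowledge.** From the article: 6 preschools per arm, and 200 × 0.9 = 180 children per preschool. Assumed, because the article gives none of them:

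- knowledge ICC of 0.02, 0.05 or 0.10;
- baseline-to-follow-up correlation of 0.5 to 0.7 between preschools and 0.4 to 0.5 within;
- equal SD at both times, so that slope equals correlation.

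**Chance imbalance.** In score-SD units, a preschool mean has variance V = ICC + (1 − ICC)/180. The difference between arms has SD = √(2V/6). The share that reaches the estimate is this SD times the slope.

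| ICC | V | Imbalance SD | × 0.5 | × 0.7 |
|---|---|---|---|---|
| 0.02 | 0.0254 | 0.092 | 0.046 | 0.064 |
| 0.05 | 0.0553 | 0.136 | 0.068 | 0.095 |
| 0.10 | 0.1050 | 0.187 | 0.094 | 0.131 |

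The formula ignores that allocation is balanced within county (3 and 3 in each), so it overstates the imbalance to the extent that the counties themselves differ in knowledge.

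**Precision.** Adjusted variance = ICC(1 − r_b²) + (1 − ICC)(1 − r_w²)/180, with r_b the between-preschool and r_w the within-preschool correlation. SE ratio = √(adjusted / V).

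- ICC 0.02, r_b = 0.5, r_w = 0.4: (0.0150 + 0.00457)/0.02544 = 0.769, ratio 0.88
- ICC 0.02, r_b = 0.7, r_w = 0.5: (0.0102 + 0.00408)/0.02544 = 0.561, ratio 0.75
- ICC 0.10, r_b = 0.5, r_w = 0.4: (0.0750 + 0.0042)/0.1050 = 0.754, ratio 0.87
- ICC 0.10, r_b = 0.7, r_w = 0.5: (0.0510 + 0.00375)/0.1050 = 0.521, ratio 0.72

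The SE falls by 12 to 28% against an analysis with no covariates. At the level of the child alone, the residual variance is multiplied by 1 − r²: 0.91, 0.75 and 0.51 for r = 0.3, 0.5 and 0.7.

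**Outcome type.** Assume a 0 to 18 number correct with independent items and proportion correct p. Variance over mean is 1 − p, that is 0.5, 0.3 and 0.1 at p = 0.5, 0.7 and 0.9, against 1 for a Poisson count. A Poisson with the same mean puts 0.2%, 5.5% and 27.4% of its probability above 18. Scores of zero have probability (1 − p)^18, about 0.16% at p = 0.3 and less above that, so there is no excess of zeros to model.

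**The case against.** The strongest reply is that the covariate sentence is a condensed list written around the injury outcome, and that an analysis plan could add baseline knowledge. A longitudinal GEE or GLMM could also take the baseline score in as a repeated measure. Both are possible, but the text says neither, and it names the knowledge score as an outcome of these models. As published, the adjustment for knowledge lacks its baseline.

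A second reply concerns size, and it stands. The ICCs and correlations are assumptions. The 12 to 28% compares with an unadjusted analysis, whereas the plan already adjusts for socio-demographic variables. Its subgroup paragraph counts age, grade, caregiver education and income among socio-demographic factors. In children aged 3 to 6 these probably carry part of the information in baseline knowledge, so the additional gain is smaller.

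Two stronger readings are tempting, and the documents support neither.

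- A reader might infer that the knowledge estimate is biased, or that any baseline imbalance enters it in full. Randomization keeps the estimate unbiased on average, and imbalance enters only in proportion to the slope.
- A reader might infer that a Poisson model is planned and that standard errors will be 1.8 to 2.2 times too wide, from √(1/(1 − p)) = 1.83 at p = 0.7 and 2.24 at p = 0.8. The article names no family or link, and a binomial or Gaussian GEE or GLMM fits its wording. Zero-inflation is conditional on need. The ratio also presumes independent children and model-based Poisson errors. Robust GEE errors come from the observed spread rather than from the assumed family, and in a GLMM dominated by preschool variance the child-level part matters little.

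The 0 to 18 range is itself inferred from the 18 items, since no scoring rule is given.

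**Conclusion.** The point holds as a matter of precision on a secondary outcome. Knowledge is measured at baseline in both arms, and the stated adjustment for the knowledge score uses baseline injury events and omits baseline knowledge. Under the assumptions above, a chance imbalance with an SD of about 0.09 to 0.19 score SDs goes unadjusted. Of this, roughly 0.05 to 0.13 carries into the estimate. The forgone reduction in SE is at most about 12 to 28%, and less given the covariates already planned. The article's text does not support a claim of bias on average, of standard errors inflated by a count model, or of any effect on the primary analysis or the 2378. The grouping with count outcomes calls for clarification only.

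**What to change.** In the Data analysis plan, add a sentence for the knowledge outcome: the GEE or GLMM, clustered by preschool, includes the matching baseline knowledge score (the theme score for a theme analysis, the total for the total) in place of or alongside baseline injury events.

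As a clarification, state the scoring rule. Say that the score is analysed as a bounded number correct, with a binomial or beta-binomial model or a linear one, and that Poisson and zero-inflated models are kept for injury event counts.

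The cost is a change of wording made before analysis. The baseline score is already scheduled for collection in both arms, and the sample size and the primary analysis do not change.

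### For the supportive injury-count analysis, the optional switch to zero-inflation models can replace the overall ratio of mean injury events with coefficients that do not measure it (minor; cheap to fix)

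*Protocol article*

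**What the plan says.** All references are to the protocol article.

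- **Data analysis plan.** GEE and GLMM are to assess the overall effect, for a binary outcome (any injury in the study period) and for counts: "quantitative count outcomes (number of unintentional injury events and injury prevention knowledge score) at the individual level will be analyzed using these models". The paragraph closes with "Zero-inflation models will be used when needed". It does not say what would make such a model necessary, which form it would take, or which arm parameter would then carry the conclusion.
- **Primary outcome measure.** The primary incidence rate is the number of children with a new injury over the year divided by all children, so it is a proportion. The number of events is recorded at each quarterly survey, but it is not itself named as a primary or secondary outcome.
- **Sample size.** Control incidence is set as follows: "unintentional injury incidence among preschoolers aged 3–6 years old in the study sites over a 12-month period will be 30" per cent. The effect is worded as "we estimated the effect size of the Safety Experience Room intervention will be 0.75 (incidence rate ratio"). The stated result is that "a minimum sample size of 2378 preschoolers is sufficient to achieve statistical power of 80% at the significance level of 0.05".

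**The concern.** For event counts, the natural question is whether the mean number of injuries per child is lower in the intervention arm. A log-link GEE estimates that directly, as one ratio of means.

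A standard zero-inflated model describes two things: the chance that a child belongs to a latent at-risk class, and the event rate within that class. With arm in both parts, the effect is divided between two coefficients with two different null hypotheses, and neither null is equality of mean injury counts. The usual output shows the exponentiated count coefficient as a rate ratio, and it is easily read as the overall effect.

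The switch would also be decided after looking at the data, so the parameter tested for this outcome could depend on the observed distribution. At stake is a supportive result that shows little or no effect although injuries fell by a quarter.

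**Working it through.** **1. What the 0.75 was used for.** Inputs from Sample size: 0.30 in control; 0.75 × 0.30 = 0.225 in intervention; "An intra-class correlation (ICC) of 0.005 within a cluster size of 200 children per preschool was estimated"; "we conservatively estimate a maximum attrition rate of 10% over the 12-month follow-up time period"; 80% power. The tests are two-sided at 0.05 (Data analysis plan).

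- Per arm, two proportions, unpooled: (1.960 + 0.842)² × (0.30 × 0.70 + 0.225 × 0.775) / 0.075² = 536.34
- Design effect: 1 + 199 × 0.005 = 1.995
- Total: 2 × 536.34 × 1.995 = 2140.0; divided by 0.9 = 2377.8, rounded up to 2378

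The plan's figure is reproduced. Poisson event-rate formulas give about 3248 (difference scale) or 3270 (log scale). So 0.75 served as a ratio of proportions, and the count analysis has no power calculation of its own.

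**2. What the coefficients measure.** Let *s* be the share at risk and λ the Poisson mean among those at risk. Then

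- overall mean = *s* × λ, so overall ratio = (*s*₁/*s*₀) × (λ₁/λ₀).

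With arm in both parts and no other covariates, the fit in each arm solves

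- λ / (1 − e^(−λ)) = mean count among injured children
- *s* = P(at least one injury) / (1 − e^(−λ)).

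The share of children injured does not enter λ. Multiplying the two solutions gives *s* × λ = P(at least one injury) × mean among injured = the arm's sample mean. The overall ratio derived from this model is therefore the ratio of raw means; the information is lost only if the count coefficient is read alone.

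**3. Size, by simulation.** Effective children per arm: 2378 × 0.9 / 2 / 1.995 = 536. The at-risk share is not in the document. It is assumed to be 0.4 to 0.7, with λ = −ln(1 − 0.30/*s*), from 1.39 down to 0.56, so that 30% of control children are injured. Every scenario has a true overall ratio of 0.75; 3000 runs each, Wald tests at 1.96.

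| At-risk share | Effect acts through | Count-part ratio (median) | Power, count part | Power, overall ratio | Power, binary outcome |
|---|---|---|---|---|---|
| 0.4 | share at risk | 1.00 | 5% | 66% | 80% |
| 0.5 | share at risk | 1.00 | 5% | 68% | 80% |
| 0.6 | share at risk | 1.00 | 5% | 68% | 80% |
| 0.7 | share at risk | 0.99 | 5% | 70% | 80% |
| 0.4 | both equally | 0.87 | 20% | 69% | 59% |
| 0.5 | both equally | 0.87 | 14% | 68% | 64% |
| 0.6 | both equally | 0.87 | 11% | 70% | 68% |
| 0.7 | both equally | 0.87 | 9% | 71% | 70% |
| 0.4 | rate only | 0.75 | 61% | 70% | 33% |
| 0.5 | rate only | 0.75 | 39% | 70% | 47% |
| 0.6 | rate only | 0.74 | 30% | 72% | 56% |
| 0.7 | rate only | 0.75 | 23% | 73% | 61% |

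A repeat run gave 24 to 61% for the count part in the rate-only rows. The difference is simulation error: √(0.23 × 0.77 / 3000) is about 0.8 points.

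**4. Other readings of the same model family** (first two: 600 runs per cell, error about 2 points).

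- *Joint two-degree-of-freedom test of both arm terms:* 68 to 71% power when the effect is in the share, 63 to 68% when it is in the rate.
- *Arm in the count part only:* power 74 to 78% and ratio 0.74 to 0.75 when the effect is in the rate. When it is in the share, the model is misspecified: ratio 0.77 to 0.86, power 29 to 65%.
- *Negative binomial counts without structural zeros (dispersion 0.3, 0.5, 1.0), fitted by zero-inflated Poisson with arm in both parts:* count ratio 0.80, 0.78, 0.76; power 56%, 44%, 31% against 54%, 64%, 69% for the overall ratio. The count part is not weaker in the first case, but its model-based standard error is not reliable under this misspecification.

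**The case against.** The strongest reply is that the sentence fixes no specification. It does not say that arm enters both parts, that the count coefficient would be read alone, or that the model would displace GEE and GLMM. Trigger and model form may properly sit in an analysis plan that is not shown. That stands: the missing detail is not the point, and the 5% figure belongs to one specification combined with one mechanism. What remains is that the text allows the observed data to move the analysis to a model family whose usual arm coefficients do not answer the overall question the paragraph sets.

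A reader might infer more, and the documents do not support it:

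- *That the primary result is at risk.* The primary outcome is binary, and a zero-inflation model does not apply to it.
- *That the planned incidence rate ratio would go untested.* Despite its name, 0.75 reproduces 2378 only as a ratio of proportions.
- *That the switch is likely because about 70% of children have no injury.* A plain Poisson with mean 0.357 gives e^(−0.357) = 0.70, so that share alone shows no excess of zeros.
- *That no one could tell whether injuries fell.* Where the count coefficient is null, fewer children are injured, and the binary analysis has 80% power.
- *That every zero-inflation analysis misses the effect.* Step 4 shows otherwise.

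**Conclusion.** The point holds for the supportive analysis of the number of injury events only. With arm in both parts, the count coefficient is not the overall ratio of mean events. At a true overall ratio of 0.75 it loses about 61 to 65 points of power (5% against 66 to 70%) when the programme changes who is at risk, and about 9 to 50 points (61% against 70%, down to 23% against 73%) when it changes the rate among those at risk.

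These sizes rest on an assumed at-risk share of 0.4 to 0.7, Poisson counts within the at-risk class, and clustering handled through the plan's design effect rather than simulated preschools. The normal critical value is generous for 12 preschools, so absolute powers are approximate; the contrast between the two parameters is what matters. Severity is minor: a cheap improvement to one sentence.

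**What to change.** Replace the zero-inflation sentence with wording to this effect: *The effect measure for the number of injury events is the overall (marginal) ratio of mean events between arms, estimated by a log-link GEE clustered on preschool, with a robust variance suited to a small number of clusters. It is retained whatever the share of zeros. Any zero-inflated model is supplementary and is also reported as a marginal rate ratio.*

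The cost is one sentence. Overdispersion is handled by the robust variance, and a high share of zeros does not in itself invalidate a comparison of means. The one loss is that the split into whether a child was injured and how often becomes descriptive for this outcome; the binary primary outcome already covers the first half.

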**Methods and analysis:**

A single-blinded, 12-month follow-up, parallel-group cluster randomized controlled trial with a 1:1 allocation ratio will be implemented in two selected counties. In total, at least 2378 rural preschoolers aged 3–6 years old will be recruited from 12 preschools, 6 in Yang County and 6 in Shicheng County. Clusters will be randomized at the preschool level and allocated to the control group (routine school-based education) or the intervention group (routine school-based education plus the Safety Experience Room education). External support strategies will be implemented by local partners to minimize attrition. Data collection will be conducted at baseline and then every 3 months during a 12-month follow-up time period. Intention-to-treat (ITT) data analysis will be used. Generalized estimation equations (GEE) will evaluate the effectiveness of the program and generalized cost-effectiveness analysis (GCEA) will evaluate the cost-effectiveness of it. A per-protocol (PP) sensitivity analysis will assess the robustness of ITT results. Subgroup analyses will be performed to evaluate the impact of socio-demographic factors on the intervention effect, following the same strategies as the primary analyses.

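### The subgroup analyses aim to detect effect modification, but the stated method is the primary strategy, which has no between-subgroup comparison and no safeguard against over-reading chance differences

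*Protocol article*

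**What the plan says.** The Data analysis plan section states the aim: "Subgroup analyses will be performed to assess the impact of socio-demographic factors on the intervention effectiveness". It names five factors, "including sex and age of children, grade level of preschoolers, education level of preschooler caregivers, and household income per capita in the prior 12 months", without levels or cut-points. The method follows: "Subgroup analyses will follow the same statistical strategies for primary analyses". The abstract (Methods and analysis) agrees: "following the same strategies as the primary analyses".

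The same section describes the strategies to be followed:

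- Chi-square, t or Wilcoxon tests at each time point, which "will be used to examine the differences in outcome measures between intervention and control groups for categorical and continuous variables, respectively".
- Trend tests or ANOVA for change within each group over the follow-up visits.
- GEE and GLMM "to evaluate the overall effectiveness of the intervention after adjusting for socio-demographic variables, engagement, and baseline injury events".

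One rule covers every test: "All statistical tests will be two-sided, with the level of 0.05 considered statistically significant". The article does not call the subgroup results exploratory.

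**The concern.** Whether a factor changes the effect is a question about the difference between the effects at its levels. None of the listed procedures estimates or tests that difference. The first and third compare arms, the second looks within an arm over time, and in the models the socio-demographic variables serve only as adjustment covariates. Repeating these steps by subgroup gives one arm comparison per level, each judged at 0.05.

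The sample was sized for the overall effect, so each level is underpowered. A perfectly uniform effect will then often be significant at one level and not at another. At stake is whether a statement such as *works in girls but not in boys* would rest on evidence or on chance. The primary conclusion is not at stake.

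**Working it through.** **Inputs.** From the Sample size section: control incidence 30%, ratio 0.75 (so 22.5%), ICC 0.005, cluster size 200, attrition 10%, N = 2378, and N described as "sufficient to achieve statistical power of 80% at the significance level of 0.05". From Preschool recruitment: 6 preschools per arm. Equal-sized levels are my assumption, since the article gives no cut-points.

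**1. The plan's own figure.**
- Variance term: 0.30×0.70 + 0.225×0.775 = 0.384375.
- Per arm before clustering: (1.960 + 0.842)² × 0.384375 / 0.075² = 7.849 × 0.384375 / 0.005625 = 536.3.
- Design effect: 1 + 199×0.005 = 1.995.
- Total: 2 × 536.3 × 1.995 / 0.90 = 2377.8, i.e. 2378.

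The stated N reproduces. It powers the overall comparison only.

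**2. Power within a level.** Analysed children: 2378 × 0.90 = 2140, or 178.35 per preschool. With m children of one level per preschool:
- design effect = 1 + (m − 1)×0.005
- SE = √(design effect × 0.384375 / (6m))

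| | Two levels | Three levels |
|---|---|---|
| m | 89.2 | 59.5 |
| Design effect | 1.441 | 1.292 |
| SE | 0.0322 | 0.0373 |
| 0.075 / SE | 2.33 | 2.01 |
| Power, critical value 1.96 | 0.64 | 0.52 |
| Power, critical value 2.228 (t, 10 df) | 0.54 | 0.41 |

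The second critical value allows for 12 preschools (12 − 2 = 10 df). Both power rows use a normal approximation for the estimate.

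**3. Correlation between levels.** All levels sit in the same 12 preschools, so their estimates share the preschool effect. The correlation is m×0.005 / design effect:
- two levels: 0.446 / 1.441 = 0.31
- three levels: 0.297 / 1.292 = 0.23

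**4. Chance of discordant verdicts under a uniform effect.** I drew correlated normal estimates with these means and correlations (2 million draws) and counted trials in which some but not all levels were significant.

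| | Critical value 1.96 | Critical value 2.228 |
|---|---|---|
| Two equal levels | 37% | 40% |
| Three equal levels | 64% | 62% |

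A beta-binomial simulation of 20,000 trials (6 preschools per arm, ICC 0.005, critical value 1.96) gave 37% for two equal levels and 43% for a 30:70 split.

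**5. The direct test.** In that simulation a test of the difference between the two level-specific effects rejected in 4.8% (equal split) and 5.3% (30:70) of trials. That is the nominal rate, as it should be when the effect is uniform.

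**6. What the direct test can and cannot do.**
- Two equal levels: the shared preschool effect cancels, so the SE of the difference in effects is √(2 × 0.995 × 0.384375 / (6×89.2)) = 0.038.
- A difference in effects of about 2.80 × 0.038 = 0.106 is needed for 80% power. That exceeds the whole planned effect of 0.075.
- Five interactions at 0.05, if independent: 1 − 0.95⁵ = 0.226, about a 23% chance of at least one false positive.

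**The case against.** The strongest reply is that the article does not say arms will be tested separately within each level. The primary strategies include GEE and GLMM, which take an arm-by-factor term easily, and the aim is worded as effect modification. Interaction terms, cut-points and exploratory labels are commonly left to the analysis plan, which is not shown.

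Part of this stands. The wording does not forbid an interaction, and missing cut-points are no fault here. But the article is not silent on method. It states one, in two places, and that method contains no between-level comparison. An analysis plan that followed it faithfully would not answer the question set one sentence before.

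Three stronger readings are tempting but not supported:

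- **That chance differences will be reported as effect modification.** This is a prediction. The article gives no rule for interpreting subgroup results. What can be said is that it offers no safeguard.
- **That dissemination would be misdirected.** The Interventions and Discussion sections tie dissemination to the programme proving feasible, effective and affordable overall, not to any subgroup.
- **That discordance would be about 46–50% for two levels and 73–75% for three.** Those figures follow from treating levels as independent, for example 2 × 0.645 × 0.355 = 0.458. The levels share preschools, so the lower figures in the working apply.

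**Conclusion.** The point holds as a mismatch between aim and method. The stated strategy does not test whether the effect differs between levels, and nothing guards against reading a significant and non-significant pair as a subgroup effect. Under a uniform effect of the planned size, separate tests disagree in roughly four trials in ten for a two-level factor and six in ten for a three-level factor, against about one in twenty for a two-level interaction test.

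These figures rest on the protocol's planning values, equal-sized levels, the same incidence at every level, 12 preschools of equal size and a normal approximation. A fitted GEE with only 12 clusters may behave somewhat differently, but not enough to reverse so wide a contrast. The matter is secondary and should be corrected before analysis.

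**What to change.** Replace the method sentence in the Data analysis plan section, and align the abstract, along these lines:

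> *For each of the five factors, an arm-by-factor interaction will be added to the cluster-adjusted GEE or GLMM used for the primary outcome. The interaction estimate, its 95% confidence interval and p-value are the subgroup result, and any claim of effect modification will rest on them. Effects within levels will be shown with confidence intervals as supporting description. The five interaction analyses are exploratory.*

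The exploratory label is needed because N was set for the overall effect and, even with interaction tests, the 23% chance of at least one false positive over five factors remains.

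The cost is one sentence and one interaction per factor on data already to be collected. Design, sample size and primary analysis do not change. The downside is low power for interactions and fewer nominally significant subgroup claims.
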